## SUBJECTS AND RECRUITMENT

The characteristics for participants in the RELIEF study are listed below. As noted above, we have already completed testing on 18 men (total  $n=27$ ) and 31 women (total  $n=33$ ) in Experiment 2 of the RELIEF study (i.e., parent R01). Once completed, the data collected during the seated trunk perturbations will be used to characterize sex differences in trunk stiffness in chronic LBP participants who fit a modified clinical prediction rule for spinal manipulation. These data will be compared to a sample of matched healthy controls. Finally, the influence of sex on changes in trunk stiffness in response to spinal manipulative therapies will be assessed.

## Inclusion criteria

Participants must meet all of the following inclusion criteria to participate in this study:

- Between 18 to 45 years of age.
- Answer no to the following questions:
  - Have you had low back pain constantly or on most days for the last three months?
  - Has your back pain caused you to seek care or consultation from a health care provider?
- Average pain intensity, assessed using the Numerical Pain Rating (NPR) scale over the past week = 0 on a 0-10 numerical pain scale
- Roland Morris Disability Questionnaire score = 0
- Exhibit 3 of 4 of the following findings reported in the clinical prediction rules for spinal manipulation
  - No symptoms distal to the knee
  - FABQ work subscale score <19
  - At least 1 hypo-mobile lumbar spinal segment
  - At least 1 hip > 35 degrees internal rotation range of motion

For this supplemental grant application, we will recruit an additional 60 healthy participants with no history of LBP (i.e. no interruptions in play or work due to back pain, or visits to any healthcare provider secondary to back pain in the past 1 year) and who are matched on sex, age ( $\pm 3$  years), height ( $\pm 2$  inches), and weight ( $\pm 10$  lbs) to the participants recruited into **Experiment 2** of the RELIEF study. We will apply the same exclusion criteria to the control group as is used for the RELIEF study LBP participants. See table below.

## Exclusion criteria

Participants must not have any of the following exclusion criteria to participate in this study:

- Have a personal history of the following neurological disorders: Alzheimer's, Amyotrophic Lateral Sclerosis, Multiple Sclerosis, Parkinson's, or Stroke.
- Have a personal history of the following cardiorespiratory disorders: Congestive heart failure, Heart attack in past 24 months.
- Have a personal history of the following musculoskeletal disorders: Rheumatoid Arthritis, pathologic fractures of the spine, avascular necrosis or osteonecrosis, severe osteoarthritis. Including a history of spine surgery or a hip arthroplasty.
- Have active cancer.
- Be Blind.
- Have used narcotics or muscle relaxants within 30 days prior to study enrollment.
- Report being pregnant.
- Have a body mass index greater than 35 kg/m^2.
- Have clinical depression (i.e., subjects who score 24 or higher on the Center for Epidemiology Depression Scale).
- Current drug or alcohol use or dependence that, in the opinion of the PIs, would interfere with adherence to study requirements

## Hypothesis Testing: Aim 1

Hypothesis 1.1. Male participants with chronic LBP will present with increased stiffness compared female participants with chronic LBP

Hypothesis 1.2. Participants with chronic LBP will present with increased stiffness compared healthy controls.

Separate 2 Group (Chronic LBP, Matched Healthy Control) x 2 Sex (Male, Female) mixed-model MANOVAs will be conducted on trunk stiffness measures.

## Hypothesis Testing: Aim 2

Hypothesis 2.1. There are no net sex effects of spinal manipulation on trunk stiffness.

Hypothesis 2.2. Both manipulative interventions will decrease passive trunk stiffness as evidenced by the trunk's initial mechanical response to multi-directional trunk perturbations.

Separate 3 Group (Manipulation, Mobilization, Sham Laser) x 2 Gender (Male, Female) x 3 Time (Baseline, Immediately following initial treatment, 48 hrs post-3 weeks of treatment) mixed-model MANOVAs will be conducted on trunk stiffness measures.

**Specific Aim 3.** To examine the effects of sex and posture on trunk stiffness.

**Hypothesis 3.1.** Healthy Male participants will present with increased trunk stiffness compared to healthy female participants.

**Hypothesis 3.2.** Trunk stiffness will be greater in sitting compared to standing.

Separate 2 Sex (Male, Female) x 2 Posture (Male, Female) mixed-model MANOVAs will be conducted on trunk stiffness measures.

**Specific Aim 4.** To examine the effects of sex and trunk displacement from internally generated trunk perturbations.

**Hypothesis 4.1.** Healthy Male participants will present with less trunk displacement during internally generated trunk perturbations compared to healthy female participants.

Separate 2 Sex (Male, Female) mixed-model MANOVAs will be conducted on trunk displacements.

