Passive trunk stiffness in three cardinal planes during unanticipated seated trunk perturbations will be measured in chronic LBP participants enrolled in the RELIEF study (Experiment 2) and a healthy control group (matched for gender, age, height, and weight)- recruited for the sex/gender differences supplement.

**Specific Aim 1.** To examine the effects of sex and chronic LBP on passive trunk stiffness. H1.1. Male participants with chronic LBP will present with increased stiffness compared female participants with chronic LBP. H1.2. Participants with chronic LBP will present with increased stiffness compared healthy controls.

**Specific Aim 2.** To examine sex differences in the effects of spinal manipulation on passive trunk stiffness. H2.1. There are no net sex effects of spinal manipulation on trunk stiffness. H2.2.Both manipulative interventions will decrease passive trunk stiffness as evidenced by the trunk’s initial mechanical response to multi-directional trunk perturbations.

**Specific Aim 3.** To examine the effects of sex and posture on trunk stiffness.

**Specific Aim 4.** To examine the effects of sex and trunk displacement from internally generated trunk perturbations.

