## NUMBER OF SUBJECTS AND POWER

The primary dependent variable (DV) for the **Experiment 2** group in the RELIEF study is the short-latency stretch reflex amplitude. Our preliminary work indicates that spinal manipulation reduces stretch reflex amplitude in individuals with chronic LBP who exhibit an audible joint sound by 30% from 0.56 to 0.39.[61] In study participants with no audible joint sound, there was a non-significant 10% increase from 0.62 to 0.68. The baseline standard deviation was 0.25 for both groups. We assumed manipulation would result in a 25% reduction 2-days following a course of treatment and a 20% reduction 4-weeks post course of treatment. Given our pilot data indicating the importance of cavitation, we assumed smaller reductions in stretch reflex amplitudes at each time point for the joint mobilization treatment arm. (i.e., 28, 23, and 18% reductions at the three endpoints). Finally, we assumed that Sham Control would have the same mean (0.68) at each testing point. Based on these data, in order to achieve adequate power, Experiment 2 required a total of 60 participants with chronic LBP that met a modified clinical prediction rule for spinal manipulation. Due to the greater prevalence of LBP in women, our sample for Experiment 2 will consist of 33 females and 27 males.

To address aim 1, we will recruit 60 healthy participants with no history of LBP matched on gender, age ( $\pm 3$  years), height ( $\pm 2$  inches), and weight ( $\pm 10$  lbs) to the LBP group. A recent paper by Vazirian et al reported large effects sizes ( $\eta^2=0.425$ ) for sex differences in sagittal plane trunk stiffness in healthy participants.[65] Based on these data our sample of 120 participants (60 participants LBP, 60 matched controls) will provide power of 0.85 to determine an interaction of sex by back pain group for trunk stiffness at  $p<0.05$ .

Given that our initial power estimates for the parent R01 (i.e., RELIEF study) were designed to detect gender differences as well as treatment effects on trunk onset muscle latencies, and assuming similar effect sizes for our trunk stiffness measures, 60 participants with chronic LBP should provide sufficient power for the stiffness measures in aim 2 of this application.

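### The Aim 1 analysis does not use the matching of controls to patients; if stiffness is still correlated within pairs after sex, the group contrasts lose precision

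*Supplement*

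**What the plan says.** The matching is described in the protocol (version 6.0) in the Précis (Sample Size and Population), in Section 4.2 and in the supplemental appendix. Under Number of Subjects and Power, the appendix says "we will recruit 60 healthy participants with no history of LBP matched on gender, age", with calipers of 3 years for age, 2 inches for height and 10 lbs for weight. Specific Aims describes "a healthy control group (matched for gender, age, height, and weight"). The numbers are one to one: "our sample of 120 participants (60 participants LBP, 60 matched controls").

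For Aim 1 the analysis is one sentence: "Separate 2 Group (Chronic LBP, Matched Healthy Control) x 2 Sex (Male, Female) mixed-model MANOVAs will be conducted on trunk stiffness measures". H1.2, which compares patients with controls, depends on this model. Section 9.5 refers the supplement's analysis to the appendix, so no other section adds a pair term, pair differences or covariates.

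The power statement says that the sample "will provide power of 0.85 to determine an interaction of sex by back pain group for trunk stiffness". It mentions no within-pair correlation.

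**The concern.** Matching on variables related to the outcome usually makes the two members of a pair more alike than two unrelated people. Body size is a plausible source of this here: under Assessing Trunk Stiffness, the applied load scales with the participant's anthropometry, and trunk mass is estimated in the same equation as stiffness.

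A model with only Group and Sex treats all 120 people as independent once sex is accounted for. Any similarity due to age, height and weight stays in the error term of the group comparison. The intervals for H1.2 and for the Group by Sex interaction would then be wider than the design allows, and recruiting within three extra calipers would bring little return in precision.

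**Working it through.** **The plan's own figure.** The power of 0.85 does not reproduce from its stated input. An η² of 0.425 gives f² = 0.425/0.575 = 0.739 and a noncentrality of 120 × 0.739 = 88.7, so power exceeds 0.999. Power of 0.85 with N = 120 needs f = 0.276, or d = 0.55. The cited η² is also "for sex differences in sagittal plane trunk stiffness in healthy participants", a sex main effect and not an interaction. That is a separate matter and does not decide this point. I use d = 0.55 only as a second reference value below.

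**Inputs.**
- From the appendix: 60 patients and 60 controls; "our sample for Experiment 2 will consist of 33 females and 27 males", which the controls follow by matching; a test level of 0.05, taken as two-sided.
- Assumed: r, the within-pair correlation after sex, at 0, 0.1, 0.3 and 0.5; a group difference of d = 0.4 in within-sex SD units.

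**Formulas (SD = 1).**
- Planned SE of the group difference: √(2/60) = 0.183. The residual variance of the 2 × 2 model still averages 1 when pairs are correlated, so this does not change with r.
- True SE, which is also the pair-aware SE: √(2(1−r)/60).
- Ratio of pair-aware to planned SE: √(1−r).
- Interaction SE: √(2/33 + 2/27) = 0.367 as planned, times √(1−r) when pair-aware.
- Pair-aware power: noncentral F with 1 and 58 df and noncentrality d²/[2(1−r)/60].
- Planned power and type I error: the 116-df test applied to an estimate whose true SE is the smaller one. Planned power therefore also rises a little with r.

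**Example, r = 0.3.** True SE = 0.183 × √0.7 = 0.153. The noncentrality is 0.16/0.0233 = 6.86, which gives power 0.73.

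| r | SE ratio | Planned SE too wide by | Actual type I error, planned | Power d = 0.4, planned | Power d = 0.4, pair-aware | Interaction SE, pair-aware |
|---|---|---|---|---|---|---|
| 0 | 1.00 | 0% | 0.050 | 0.58 | 0.58 | 0.367 |
| 0.1 | 0.95 | 5% | 0.039 | 0.59 | 0.62 | 0.348 |
| 0.3 | 0.84 | 20% | 0.02 | 0.60 | 0.73 | 0.307 |
| 0.5 | 0.71 | 41% | 0.006 | 0.62 | 0.86 | 0.260 |

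At d = 0.4 the gain is about 0.03, 0.13 and 0.24 for r of 0.1, 0.3 and 0.5. At r = 0 pairing costs less than 0.01. At d = 0.55 the gains are smaller: 0.864 to 0.879, 0.893 to 0.944 and 0.930 to 0.988.

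Simulation with 33 female and 27 male pairs agrees. At r = 0.3 the planned model's mean SE was 0.183, the true SD of the estimate was 0.153, and the planned test rejected a true null in about 2% of runs.

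**The case against.** **The size rests on an undocumented correlation.** This stands. A reader might infer that the planned standard errors are too wide as a matter of fact. The documents do not support that, because they report no within-pair correlation. If r is zero after sex, the planned analysis is right and pairing loses a little power.

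**Sex may already carry most of the similarity.** This stands as a limit on size. If sex explained 42.5% of the variance and nothing else linked the pair, the pair members would correlate at about 0.4 before sex is removed, yet the planned model and a paired analysis would both have power of about 0.81 (difference of 0.4 total SD). A t-test without sex would have 0.61. So r must be read as what is left after sex, and comparison with a t-test that omits sex would overstate the gain.

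**The matching may not be individual.** The documents never write of pairs or individual matching, and no pair identifier is described. Equal numbers and numeric calipers, which have meaning only relative to a particular patient, make one-to-one matching the natural reading. It remains an inference.

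**The plan does say mixed-model.** That label cannot be taken to mean a pair effect. The appendix also uses it for Aim 4, whose only factor is Sex and which has no patient-control pairs.

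**No false claim would follow.** Correct. With complete pairs the group estimate is unbiased, and for positive r the test rejects too seldom.

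**Conclusion.** The point holds as a conditional loss of efficiency. As written, the Aim 1 model drops the matching on age, height and weight. If r after sex is positive, the planned SE for H1.2 and for the Group by Sex interaction is inflated by 1/√(1−r): 5%, 20% and 41% at r of 0.1, 0.3 and 0.5. Those values of r, and d = 0.4, are assumptions.

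It would be wrong to conclude that Aim 1 is biased or prone to false positives, or that the wider study is affected. H1.1 compares men and women among patients only, Aim 2 uses patients only, and Aims 3 and 4 use healthy participants only. The RCT and the parent mechanistic comparisons do not involve the controls. Severity is low to moderate and confined to the supplement.

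**What to change.** Add a random intercept for matched pair to the Aim 1 model, with Group varying within pair and Sex between pairs. Keep any participant without a partner in the same model, which accommodates single members. Unmatched participants are a real possibility: Subjects and Recruitment reports 49 of the 60 patients tested (18 men and 31 women), and the Timeline starts recruiting controls while Experiment 2 is still being completed.

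If the patient-control links were not recorded, adjust for age, height and weight in all participants. Applying those covariates only where a pair is incomplete would not be one coherent model.

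Leave the planned set of stiffness measures and the approach to multiplicity as they are.

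The cost is analysis wording, provided the links exist or can be rebuilt from the matching records; the documents do not confirm this. The statistical cost is under 0.01 of power if r is near zero.

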## 9.2 Sample Size and Randomization

### **Sample Size Calculation for Mechanistic Component**

For each primary hypothesis, sample size to achieve the power of 0.80 was computed using Monte Carlo simulation studies. For all simulation studies, the following were assumed:

- The Type I error rate (the alpha level) was set at 0.05 and the Type II error rate (the beta level = 1 - power) at 0.20.
- A first-order autoregressive temporal structure was assumed with  $\rho$  of -0.50.
- Holm's method was used to adjust the alpha level.
- To produce a plausible attrition rate, 10% of the computer-generated participants dropped out at either 2-days or 4-week post treatment measure completely at random; these participants contributed no scores at subsequent measures. To make the sample-size calculation slightly conservative, missing observations remained missing.
- Linear mixed effects regression (LMER) was used to analyze the data.
- To ensure the acceptable precision, each simulation study was repeated 10,000 times.
- The baseline measure was included as a covariate to improve power and precision of the test.

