## **9.5 Data Analyses**

Here we describe three stages at which both the Mechanistic and RCT data will be analyzed in the same fashion: preliminary analysis, checking assumptions, and detailed analytic approach. Data analysis regarding the supplemental research is included in the appendix.

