### **Detailed Analytic Approach:**

Linear mixed-effects regression (LMER) analyses will serve as the main analytic framework, because it offers distinct advantages in statistical power and estimation of population parameters over ANOVA or MANOVA. First, LMER easily incorporates miscellaneous factors (e.g., blocks and treatment providers) as random effects so that the variances due to those factors can be partitioned. As a result, LMER models typically offer less biased parameter estimation and can also offer higher statistical power. It can model multiple dependent variables (e.g., motor evoked potential amplitude, intracortical facilitation, and short-interval intracortical inhibition for Group 3) and test the effect of treatment for each of these dependent variables simultaneously. This modeling technique avoids alpha inflations which typically result from multiple testing. Finally, LMER's maximum-likelihood estimation allows patients with missing observations to be included in a model if the observations are missing completely at random or missing at random. This advantage is important because some degree of attrition is unavoidable given the longitudinal nature of our project. Because we will stratify our samples by sex, sex will be included in each of the models we will describe below. We will test the significant main effect of sex as well as its interaction with the Treatment factor.

- **Intention to Treat Analysis (ITT):** We will include all randomized study participants who have at least baseline endpoint assessments in our ITT analysis. The ITT analysis is our primary method for assessing outcomes, and how it is performed will be determined based on the pattern of

missingness. If the missingness is deemed MCAR, the LOCF method will be used: simply the most recent valid observation will be "carried forward" to replace the subsequent missing observations. If the missingness is deemed MAR, missing observations will remain as missing, and maximum-likelihood estimation, the default estimation algorithm of LMER, will be used to estimate these observations. If the missingness is found to be MNAR, multiple-imputed data will be used to construct LMER models.

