### **Mechanistic Component**

- Group 1 (Muscular Effects):
  - We will test whether three group means will significantly differ from each other at either OA2, OA3, and/or OA4 with the baseline value included in the model as a covariate. Following the significant treatment effect, we will perform Fisher's Least Significant Difference (LSD) to examine which group significantly differs from which without any adjustment. This analytic process will be repeated for the outcomes for the other two Groups.
- Group 2 (Spinal Effects)
  - For short-latency stretch reflex excitability, we will test whether three group means will significantly differ from each other at either OA2, OA3, and/or OA4 with the baseline value included in the model as a covariate.
  - For trunk muscle onset latencies in response to postural perturbations and lumbar motion during volitional movement tasks, EMG responses from eight trunk muscles will be recorded each. To reduce the complexity of the data, we will first perform separate principal component analysis (PCA). The scores of the first principal component (i.e., the linear combination of onset latencies of eight muscles) will then be used as the DV for the LMER analysis. We hypothesize that there are significant effects of treatment on PC scores at OA2, OA3, or OA4, after controlling for the baseline outcome value.
  - For the lumbar motion during volitional movement we will test whether three group means will significantly differ from each other at either OA2, OA3, and/or OA4 with the baseline value included in the model as a covariate.
- Group 3 (Cortical Effects)
  - For motor evoked potential amplitude, intracortical facilitation and short-interval intracortical inhibition, we will test whether three group means will significantly differ from each other at either OA2, OA3, and/or OA4 with the baseline value included in the model as a covariate.
- Exploratory Analyses
 

We will perform three exploratory analyses to examine the relationships between the changes in physiological outcomes and the changes in clinical outcomes as detailed below.

  - We will calculate Pearson product-moment correlation coefficients for parametric data and Spearman's rank correlation coefficients for non-parametric data.

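### Aim 2 of the supplement treats baseline trunk stiffness as a level of Time rather than as a covariate, so the treatment test for H2.2 is unbiased but less efficient than the data allow

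*Supplement*

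**What the plan says.** Aim 2 carries two hypotheses: no net sex effect of manipulation on stiffness (H2.1), and H2.2, "Both manipulative interventions will decrease passive trunk stiffness as evidenced by the trunk's initial mechanical response". Under Hypothesis Testing: Aim 2, the appendix specifies "Separate 3 Group (Manipulation, Mobilization, Sham Laser) x 2 Gender (Male, Female) x 3 Time (Baseline, Immediately following initial treatment, 48 hrs" after the three-week course) mixed-model MANOVAs on the stiffness measures. It names no baseline covariate and no rule for missing visits.

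The parent plan handles baseline differently. In the section 9.2 simulation assumptions, "The baseline measure was included as a covariate to improve power and precision of the test". In section 9.5, the Experiment 2 reflex outcome is tested for whether the three group means "differ from each other at either OA2, OA3, and/or OA4 with the baseline value included in the model as a covariate". Section 9.5 also chooses linear mixed-effects regression (LMER) "because it offers distinct advantages in statistical power and estimation of population parameters over ANOVA or MANOVA".

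The parent model does not reach stiffness by default, because section 9.5 says: "Data analysis regarding the supplemental research is included in the appendix". On power, the appendix says only that "60 participants with chronic LBP should provide sufficient power for the stiffness measures in aim 2 of this application". It rests this on parent estimates and on assumed similar effect sizes.

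**The concern.** The trunk perturbation test that yields stiffness is run before treatment in Experiment 2, so a baseline value exists for each randomised participant. Arms are randomised, so their expected baseline means are equal and baseline carries no information about treatment. Its only use for H2.2 is to remove between-person noise from the follow-up values.

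Making baseline a Time level fixes its weight at one, because Group x Time is a test on differences from baseline. A covariate lets the data choose the weight. Unless the correlation between visits is close to one, subtracting the whole baseline adds noise that adjustment would avoid. A real effect of manual therapy on stiffness is then more likely to be missed, in a sample fixed at 60.

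The power statement is affected too. The parent simulations that are documented assumed a baseline covariate, so their power would not carry over to this test even if the effect sizes matched.

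**Working it through.** **Inputs from the documents.** 20 per arm and alpha 0.05 (sections 3 and 9.2). Reflex-amplitude proxy (appendix, Number of Subjects and Power): SD 0.25; reductions of 30% then 25% for manipulation and 28% then 23% for mobilization; sham constant at 0.68. Section 9.2 gives the same values, including the immediate 30%. A common baseline mean of 0.56 (the baseline reported with an audible joint sound) was also tried, because active-arm baselines are not stated.

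**Assumed, because the documents give nothing for stiffness.** Visit correlation rho from 0.3 to 0.9, under compound symmetry (CS) or AR(1), with reflex effects standing in for stiffness effects.

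**The plan's own figure.** Aim 2 has no power figure to reproduce. The parent Experiment 2 figure is 0.80. A simulation with baseline-adjusted F tests at OA2, OA3 and OA4, Holm's method and 10% dropout gave 0.77 (rho 0.5), 0.72 (rho 0) and 0.88 (the printed rho of -0.50) with all baselines at 0.68. With all baselines at 0.56 it gave 0.54 to 0.68. These bracket 0.80 without identifying it, because the active-arm baselines and the exact test are not stated.

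**Single contrast.** With common variance s² at each visit:

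- change score: residual variance 2s²(1 - rho)
- baseline-adjusted: residual variance s²(1 - rho²)
- ratio = (1 - rho²) / [2(1 - rho)] = (1 + rho)/2

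A change-score test with power 0.80 at two-sided 0.05 has a standardised effect of 1.96 + 0.84 = 2.80. Dividing by the square root of the ratio gives the adjusted power:

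| rho | ratio | adjusted power |
|---|---|---|
| 0.3 | 0.65 | 0.94 |
| 0.5 | 0.75 | 0.90 |
| 0.7 | 0.85 | 0.86 |
| 0.8 | 0.90 | 0.84 |
| 0.9 | 0.95 | 0.82 |

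**The Aim 2 layout.** Monte Carlo, 4,000 runs per setting, 60 complete participants, sex and sex x group in both models, Wilks test with 4 numerator df in both. The first figure is Group x Time, which is the group test on the two changes from baseline. The second is the group test on the two follow-ups adjusted for baseline. The gain in points is in brackets.

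| rho | CS, mean 0.68 | AR(1), mean 0.68 | CS, mean 0.56 | AR(1), mean 0.56 |
|---|---|---|---|---|
| 0.3 | 0.479, 0.769 (29) | 0.446, 0.744 (30) | 0.341, 0.584 (24) | 0.301, 0.534 (23) |
| 0.5 | 0.640, 0.814 (17) | 0.584, 0.762 (18) | 0.458, 0.627 (17) | 0.411, 0.570 (16) |
| 0.7 | 0.878, 0.941 (6) | 0.821, 0.888 (7) | 0.702, 0.795 (9) | 0.635, 0.722 (9) |
| 0.8 | 0.978, 0.990 (1) | 0.953, 0.970 (2) | 0.879, 0.920 (4) | 0.836, 0.868 (3) |
| 0.9 | 1.000, 1.000 (0) | 1.000, 1.000 (0) | 0.998, 0.999 (0) | 0.989, 0.993 (0) |

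A separate run with 10% dropout, complete cases in both models and mean 0.68 agrees. CS gave 0.44 v 0.71, 0.60 v 0.78 and 0.82 v 0.89 at rho 0.3, 0.5 and 0.7. AR(1) gave 0.39 v 0.68, 0.53 v 0.71 and 0.76 v 0.82. Both tests rejected at 0.051 under the null at rho 0.5.

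**The case against.** The strongest reply is that the loss may be negligible. Stiffness is a fitted mechanical parameter from three loads in each of six directions, and one follow-up falls at the same visit as baseline. A correlation of 0.8 or more is plausible, and there the loss is only a few points or none. This stands. A reader might infer a fixed, sizeable loss, but the documents give no stiffness SD, effect or correlation to support one.

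The proxy is also not the outcome the appendix invokes. Its Aim 2 power statement points to parent estimates for onset latencies, and section 9.2 shows no such calculation. Section 9.1 lists latencies as a secondary hypothesis and bases sample size on the primary ones. One therefore cannot say that a stated Aim 2 power is wrong, only that none is shown and that the documented parent simulations used a different analysis.

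Four further readings go beyond the text:

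- Section 9.5 does not credit the baseline covariate with the advantage over MANOVA. It credits LMER, for its random effects, multiple outcomes and handling of missing data. The statement about the covariate is in section 9.2.
- The negative autocorrelation printed in section 9.2 belongs to the parent simulations. Carrying it into Aim 2 would inflate the contrast and says nothing about repeated stiffness.
- Loss of participants with a missing visit is what a classical MANOVA would do, but the appendix sets no rule. It adds nothing to the figures above.
- The Group x Time test is not biased. Randomisation protects it.

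Finally, the stated purpose of Aim 2 is sex differences in response, whereas the sizes above concern H2.2. None of this gives a reason to prefer baseline as a Time level.

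**Conclusion.** The point holds as one of efficiency. Aim 2 in effect analyses change from baseline where the parent plan adjusts for baseline. Using reflex amplitude as a proxy with 20 per arm, the loss for the overall treatment test is about 6 to 30 points of power if the visit correlation is 0.3 to 0.7, about 1 to 4 points at 0.8, and about 0 to 1 at 0.9. The design discrepancy is certain. Its size is conditional on the assumed correlation and on the proxy effects. The change is worth making because it costs nothing, not because the planned test is invalid.

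**What to change.** In Hypothesis Testing: Aim 2, replace the MANOVA for each stiffness measure with the parent LMER. The outcome is stiffness at the two post-baseline assessments: immediately after the first treatment, and after the course. The terms are treatment, sex, treatment x sex, time and treatment x time, with baseline stiffness as a covariate. Add treatment x sex x time if H2.1 is to be examined by visit. State that participants with one missing follow-up stay in the model.

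In Number of Subjects and Power, either give an Aim 2 calculation over a stated range of visit correlations, or say that power for stiffness was not calculated.

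The cost is appendix wording, with the same data and the parent's analysis framework. At version 6.0, 18 + 31 = 49 of the 60 Experiment 2 participants had been tested, the stiffness software was still to be developed, and analysis was scheduled for the third quarter of the supplement. The model could therefore be amended before any stiffness value was derived.
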